**Those in the high-intensity case management (Houston-HVIP) group will receive conditions #1-4 below:**

1. A case manager is assigned to meet with the injured patients to provide a brief assessment of psychological and social needs and individualized discharge planning bedside.
2. Coordinated referral, networking, and close follow-up with community-level violence outreach organizations from the City of Houston Mayor's Office and the Health Equity Collective that will provide outreach and counseling to victims, their family, and friends.
3. They will be referred to tailored social service programs based on the patient's needs, including assessments of social determinants of health, educational and financial needs, and subsequent referral for programs such as job training, educational support, housing assistance, or financial assistance programs for identified needs. Participants who are gang-related or violent perpetrators will be referred to the violence interrupter services with The Forgotten Third. Long-term opportunities for engagement with the trauma survivors' network within Memorial Hermann Hospital will be available and encouraged.
4. Participants in this program will receive services (either virtually or in-person based on the participant’s preference) characterized by intensity, complexity, and causal with an assigned case manager **over 6 months** to promote successful community-based program integration and completion: (a) **intensity** (≥8 participant contacts, biweekly or more frequent interactions, ≥30-minute encounters, 6+ months of follow-up), (b) **complexity** (addressing multiple social needs, involving multidisciplinary teams, providing active assistance with resource navigation, and tailoring services to individual needs), and (c) an emphasis on **enhancing causal inference** by through the use of an RCT.

**Those enrolled in the Standard of Care Program will receive the conditions #1-3 below:**

(1) A case manager is assigned to meet with the injured patients to briefly assess psychological and social needs and individualized discharge planning bedside.

(2) Resources for the patient to connect with social service programs based on the patient's needs, including assessments of social determinants of health, educational and financial needs, and subsequent referral for programs such as job training, educational support, housing assistance, or financial assistance programs for identified needs. Long-term opportunities for engagement with the trauma survivors' network within Memorial Hermann Hospital will be available and encouraged.

(3) Follow-up contacts and services from an assigned case manager **over two weeks** following discharge from the hospital to ensure that the patient has contacted the community-level violence outreach organizations.

Those who decline enrollment will receive usual hospital care and are offered services via the hospital-based social worker. The typical standard of care under current hospital guidelines includes the following conditions: stabilization for a current medical condition, referral to the hospital social worker for assessment of social concerns, and referrals for services while the patient is admitted to the hospital.

[figure not shown]
**Study Flow**

**Evaluation of UG3 Phase Activities:** Coalition meetings will be conducted in-person and virtually to accommodate all participants, while thorough note-taking ensures no loss of input. Summaries of these meetings are shared with the Community Advisory Board (CAB) members in a timely manner. One or more investigators will lead the groups ([name], [name], [name]). Participants will be compensated $50/meeting for their time. Data captured in the process will be secured on password-protected storage drives at UTHealth for ongoing data management, and Institutional Review Board approval will be obtained. We plan to hold six meetings prior to the pilot phase and at least 2 virtual meetings after the initiation of the pilot group to provide an update to the group.

**Qualitative Analysis:** We will conduct semi-structured virtual interviews with coalition members who volunteer to do the interview. These interviews will be audio-recorded and professionally transcribed. Participant names will be removed during transcription. A multidisciplinary research team will use a four-step approach to analyze qualitative data. First, the team will collectively read the transcripts collected from each interview to better understand the general themes. Through this process, a deductive codebook will be created to allow labeling of the text from the interviews. These codes will be generated in group analysis sessions until the team has agreed on all codes. Second, the team will code all the text. We will group emerging findings into categories of themes using an immersion-crystallization approach, including inductive thematic identification.^5^ Third, transcripts will be read by a second coder, and coding inconsistencies will be discussed and resolved by consensus between the two coders. Fourth, the team will consider how the findings relate to the current health literature, health services research, and intervention development.

**Quantitative Analysis:** Surveys will be conducted with coalition members to assess the feasibility and acceptability of aspects of programming, consisting primarily of Likert ratings. To determine the impact of program design, we will conduct an analysis of variance (ANOVA) based on the portion of the program being evaluated. Other analysis approaches may be incorporated if appropriate.

**Mixed-Methods Analysis:** Mixed-method findings will provide a more nuanced understanding of the effect of implemented strategies proposed in the toolkit. Analyses for each data collection method will be conducted independently to ensure unbiased interpretation. After completing those analyses, qualitative and quantitative findings will be integrated using data-triangulation techniques.^66^ Triangulating such data strengthens validity and decreases deficiencies or biases that might arise from any single method.^6–8^ Our multidisciplinary research team minimizes researcher bias by bringing experts with differing perspectives to review and critique the synthesis and interpretation of qualitative findings.

**Pilot Phase:** The ultimate assessment of the foundational work of the UG3 phase will be to perform a pilot phase of the Houston-HVIP, thus ensuring that the development of the intervention is complete and all aspects of the program are functional to the best of its capability. This will allow feedback to the coalition to enable program modification before a larger-scale implementation trial. First, all necessary agreements, operations manuals, and process flow maps will be developed and approved, and study materials, including computerized study surveys, will be created. Second, ten patients will be recruited to participate in the pilot Houston-HVIP over three months and will be randomly assigned to each condition. Patients and case managers will be interviewed after three months after recruitment for the feasibility and acceptability of the model. They will undergo semi-structured interviews in addition to the routine assessment of the Houston-HVIP. Semi-structured interviews will be evaluated as described under qualitative analysis. Results of this feasibility testing will be used to finalize the intervention and evaluation design and delivery of the UH3 phase.

**UG3 Milestones.** For a successful transition to the UH3 phase of the program, we will define milestones for critical aspects of the program. First, we expect full integration of trauma-informed care education to the hospital and staff, with at least 80% of eligible staff completing the educational module successfully. We will continue to educate qualified personnel until we have reached our goal and will leverage the coalition if needed for institutional support. Secondly, we will convene the coalition with the completion of the IM steps. These steps will serve as the metric for success as they will outline the formation and implementation of the Houston HVIP. The Health Equity Collective will serve as a support, and the Center for Health Equity will guide the IM framework to ensure completion. Finally, with the help of the coalition, completing a pilot with ten patients to demonstrate the feasibility and acceptability of the program will further show that the project is ready to move into the UH3 phase. By the end of the pilot phase, we will finalize all protocols for measuring and implementing the intervention.

**Aim 2: In the UH3 phase (2025-2028), our primary objective** is to conduct a randomized controlled trial to evaluate the effectiveness of Houston-HVIP in reducing repeat firearm violence events among adults receiving care at Memorial Hermann Hospital in Houston, Texas. This stage will include the random assignment of individuals to the primary intervention of the Houston-HVIP program or the comparison group that will receive the standard of care. A key aspect of this intervention will be assessing the impact of the Houston-HVIP program on violent re-injury and mental and behavioral health. Finally, we will aim to identify the predictors of implementation success in our model from each critical stakeholder perspective.

**Study Design.** The current study will focus on individuals that present to Memorial Hermann Hospital at the Texas Medical Center during the study period for community-based intentional firearm injury. The eligibility criteria for the study will be individuals aged 16-35 who presented for a gunshot injury stemming from community violence at Memorial Hermann Hospital, are English or Spanish-speaking, and provide informed voluntary consent or parent’s informed consent and child assent for the minor participants to participate in the study. Exclusions will be for individuals outside of this age range (i.e., below 16 or over 35 years old), those presenting for a firearm injury arising from a self-inflicted gunshot or unintentional gun violence, those declining voluntary informed consent, those who live outside of Harris County, those who are actively detained by the criminal justice systems at the time of enrollment, and for patients who speak a primary language that is other than English or Spanish, due to capacity limitations from community partners.

**Recruitment Plans:** Recruitment will occur following patient intake, and recruitment procedures will occur seven days a week. We will recruit individuals into the study and randomize them to the intervention and comparison conditions. The targeted enrollment for **the Houston HVIP program** and Standard of care are 17-18 patients per month during the recruitment window to a total of 137 (in each program). The anticipated total enrollment for both arms is 274 participants. Once target recruitment goal is achieved, enrollment will cease. Because the program is a 1 year intervention and the grant cycle for the UH3 phase is 3 years, we estimate needing 6 months after final participant has completed the program to complete data analysis. As a result, we anticipate a total recruitment window of 18 months.

Eligible patients will be identified from electronic medical records and integrated trauma databases within the hospital system to allow for real-time notification of admission to the Memorial Hermann Hospital and approached by program staff before discharge. This procedure will allow the recruitment of patients treated for gunshot wounds which are not critically injured and thus need hospital admission and eventual discharge from the hospital. This integrated notification system and a 24/7 recruitment process will allow research staff to approach and identify eligible patients for the study. The clinical team will also be provided with cards that includes a QR code (linked to the study website) and can also refer patients, and program staff will screen for eligibility. Once patients are deemed eligible, staff members will physically engage with patients at the hospital bedside to establish trust and assess the needs of the patient. The research team will coordinate with the treatment team to ensure that they are not interrupting patient care, and that timing is appropriate (i.e., not approaching a patient who is unstable or critically ill). Participation in the program will be contingent on obtaining voluntary informed written consent from the patient.

For patients who meet eligibility criteria but are discharged before engaging with a case manager at the bedside, the case manager will make up to eight follow-up attempts over two weeks using the contact information in the EMR. The case manager will attempt to reach individuals via telephone at various times and on different days of the week. Patients who decline participation at any time are no longer contacted. If a discharged patient expresses interest in participating after being contacted, arrangements will be made to meet them in person at the hospital or virtually via Microsoft Teams, Zoom, or a telephone call to discuss study details and obtain informed consent via the REDCap system. The consents will be sent to prior to the meeting to allow sufficient time for the patient/parent (for the 16 and 17 year olds) to review the consent form. UTHealth’s “Remote Consent Process and Electronic Consent Signature” procedures will be followed.

**Recruitment and Retention Plans.** We will train case managers in motivational interviewing to increase the probability of participation. Individuals will also receive a financial incentive to compensate for their time. Our training will support a patient-centered approach within the hospital system with the goal of enhancing the overall implementation and acceptance of the program. To mitigate high attrition from the study, we will use several evidence-based strategies for study retention, including interview incentives at baseline and follow-up periods, regular phone check-ins sent via text message to maintain contact, using a list of family and friends who can help maintain contact, and working closely with community partners to help maintain contact with the participant. These procedures were shown to lead to a 91% retention rate in a study of recently released prisoners in Boston over a 12-month period.^9^

**Randomization Procedure:** Participants will be randomly assigned to either the treatment or control condition using the randomization module in REDCap. After determining eligibility and obtaining informed consent, the case manager will update these participants’ status in REDCap, where the randomization process will occur.

The randomization scheme will be generated and then uploaded into REDCap under the randomization module to ensure equal allocation to the treatment and control arms. Specifically, the randomization module will utilize a blocked randomization procedure with varying block sizes to ensure that the number of participants in each group remains balanced throughout the enrollment process. The REDCap system will automatically assign participants to either the treatment or control condition based on this scheme, ensuring allocation concealment. The intervention will be administered at the individual level. This study will require voluntary, informed written/e-consent from the adult patient and from the parent(s)/LAR and an assent for the minor patient. (ages 16 and 17). Individuals who do not provide voluntary informed written consent/e-consent will not be included in either the treatment or comparison group and will not be included in the study. Once an individual participant eligible for enrollment is selected, a designated case manager can log in to the secured REDCap system and obtain a computer-generated randomization assignment in a timely manner. Authorized, unblinded individuals who need this information to provide the appropriate intervention successfully will receive an automated notification. Due to the nature of the proposed intervention, case managers will be unblinded regarding the group assignment but will be blinded to the outcome data. Participants will be partially blinded in that they will know some information about the intervention but will not be exposed to the details of the intervention or the intervention manual. The study personnel who collect or evaluate outcome data will be blinded to the intervention. Data will be collected and stored on a readily accessible dashboard hosted through REDcap and maintained by the School of Public Health throughout the project.

**Intervention Implementation.** The intervention will be implemented during the UH3 phase using a fully powered RCT with eligible participants assigned to the Houston-HVIP program or the standard of care comparison group. Ultimately, coalition members will provide input on the intervention implementation and delivery through surveys and focus groups to provide guidance on the feasibility and acceptability of the program components.

**Quantitative Data.** Data for this study will be collected through three primary sources: (1) hospital records, (2) baseline survey before hospital discharge (baseline), 3-, 6-, 9- and 12- month follow-up surveys through program completion and (3) interviews. They will receive an electronic $50 gift card upon completing the first survey and $100 for each of the follow-up surveys (3-month, 6-month, 9-month, and 12-month). Options to take the follow-up surveys at UTHealth facilities or through the community partner will also be provided. The list of variables to be included in this study is described in Table 3. We will track our primary outcome of repeat firearm violence and victimization.

**Aim 2a: To determine the impact of the community-engaged Houston HVIP program on firearm violence during the 12-month follow up period.** Our primary outcome for Aim 2a is measures of repeat firearm violence as measured by (a) return to the hospital for an intentional firearm injury, (b) self-reported firearm victimization, or (c) mortality from a firearm injury. We will use hospital admission records to identify individuals who return to the hospital system for a violent injury during the study period. Second, to capture those victims of violence that do not result in hospital readmission, we will use self-reported measures of firearm violence during the follow-up period captured using the REDCap survey. Third, we will measure mortality from a firearm injury from death records. To achieve **Aim 2b: To assess the impact of the Houston-HVIP program on reducing violent reinjury**, we will assess (a) hospital readmission data covering both adult Level 1 trauma centers in the Greater Houston area, (b) comprehensive national death record searches, and (c) self-reported information using a validated instrument.

**Aim 2c: To determine the impact of the community-engaged Houston-HVIP program on physical and behavioral health during the 12-month follow up period.** We anticipate that compared to standard of care, those enrolled in the Houston HVIP will have significantly better health as measured by (a) PTSD [PCL-2], (b) Health and Wellbeing [SF-12], and (c) Aggression [Copeland-Linder].

**Aim 2d. To identify the predictors of implementation success, including dosage, reach, fidelity, and acceptability from the perspective of gun violence victims, health care providers, and community violence intervention specialists**. Data from quantitative surveys and qualitative interviews of key stakeholders will inform an understanding of key features leading to the successful implementation of the HVIP program.

**Semi-Structured Interviews.** To understand the mechanism of the program and for a process evaluation, we will recruit a subset of patients enrolled in both the Houston-HVIP and standard of care Program conditions after the study period (*n* = 20 from each group) to conduct semi-structured interviews. This sample will provide adequate consultations from each treatment group to reach saturation.^10^ We will also conduct semi-structured interviews with n = 20 healthcare providers, community violence specialists, and case managers. The purpose of these interviews is to achieve Aim 2c: To identify the predictors of implementation success, including dosage, reach, fidelity, and acceptability from the perspective of gun violence victims, health care providers, and community violence intervention specialists. Semi-structured interviews with one or two research team members will last approximately 60 minutes and will be conducted virtually or telephonically three months [pilot group] / fifteen months [full study trial group] after the initial hospitalization. Researchers will use an interview guide composed of open-ended questions to structure the interview. Open-ended questions will allow unanticipated themes and issues to emerge and allow the participants to elaborate on their individualized experiences in their own words. Interviews will be audio-recorded and transcribed, and analyzed using thematic analysis similar to the UG3 section under qualitative analysis.

**Sample Size and Statistical Power.** We base our sample size calculation on a comparison of firearm violence between two randomization groups (Houston HVIP vs. SOC) with a two-sided alpha of 0.05. The primary outcome of firearm violence is a composite of (a) return to the hospital for an intentional firearm injury (hospital records), (b) self-reported firearm victimization (CTS-2), or (c) mortality from a firearm injury (mortality records). We will follow the participants at 3, 6, 9, and 12 months following the baseline visit and record whether the outcome occur between the visits. We will compare time to firearm violence between the two arms using a Weibull regression model for interval-censored data to account for the interval-censoring and potential loss to follow-up. A prior study among youth seeking assault-injury care at an emergency department observed a two-year rate of 59% for this composite outcome, where the reporting rates between 0-6, 6-12, 12-18, and 18-24 months were 37.5%, 25.8%, 20.5%, and 15.2% respectively^11^. This pattern suggests a potential decreasing hazard over time that can be well accounted for by a Weibull distribution, which flexibly allows for increasing, decreasing, or constant hazard shapes. We conducted simulations based on a Weibull distribution with a two-year probability of 59% in the SOC arm, corresponding to a one-year probability of 42%. To estimate the power, we generated 10,000 simulated data from this distribution, imposed interval-censoring according to the planned follow-up, added right censoring from potential attrition (patient lost to follow-up), and applied the planned Weibull regression model. Under a sample size of 274 (137 in each arm) and allowing up to 35% attrition during the follow-up, we have 80% power to detect a hazard ratio (HR) of 0.50, corresponding to a reduction from 42% to 24% in one year. The planned adjustment of important risk factors in the Weibull regression model will offer enhanced power. The planned sample size will also provide adequate power for the secondary outcomes. For example, for a continuous outcome such as SF-12, a complete sample size of 200 (100+100) allows us to detect a small to moderate between-group difference, Cohen’s d=0.40, with 80% power and a two-sided alpha=0.05 in a two-sample t-test. This calculation is conservative as the repeated measure for these outcomes provide enhanced power in the planned mixed effect model when compared to a two-sample t-test at one time point.

**Statistical Analysis.** Primary analysis will follow the intention-to-treat principle. A Weibull regression model for interval-censored data will be used to compare the risk of firearm violence between the two study groups. A two-sided alpha of 0.05 will be used to determine statistical significance. Since prespecified adjustment of important baseline covariates can provide enhanced power, the regression model will be adjusted for race/ethnicity, biological sex, and age. In addition, we plan to balance-cross case managers across the two arms to protect against potential agent effects, if any, and will adjust case manager as a fixed factor covariate in our analytic model^83^. We will carry out several secondary analyses to gain comprehensive insights and ensure the robustness of findings. Although the random enrollment of participants to the two treatment arms should ensure comparability with respect to known and unknown variables, imbalance may occur by chance. Descriptive statistics for baseline characteristics known or suspected to be associated with outcomes will be prepared for the two randomization groups. Chi-square statistics and Wilcoxon rank sum tests will be used to evaluate baseline differences between the arms for categorical and continuous variables, respectively. Any variables with baseline differences will be adjusted in secondary sensitivity analyses. Next, to assess heterogeneity of the intervention effect, we will examine interactions between the randomization group and important baseline risk factors (e.g., race/ethnicity). The corresponding interaction terms will be added individually into the regression model to examine potential effect modification. Finally, we will carry out a per-protocol analysis as a sensitivity analysis.

The secondary outcomes that are measured longitudinally (e.g., SF-12) will be analyzed using appropriate longitudinal models, such as the (generalized) linear mixed model with a suitable distribution and link function, including group, time (categorical), group by time interaction, as well as subject-specific random effects to account for the repeated measures. We will first conduct a contrast to test the intervention effect across the post-baseline time points. Group-specific means and between-group differences will be estimated at each time point with 95% confidence intervals.

In all statistical analyses, we will conduct careful checking regarding all model assumptions to ensure adequate model fit. For example, we will examine the fit of the Weibull regression model by comparing the model-based estimates to its empirical counterpart across the time-intervals (0-3, 3-6, 6-9, 9-12 months) by arm. We will also check the residual normality, homoscedasticity, and linearity for the linear mixed model. Necessary remedies will be implemented to ensure adequate model fit. We will adopt rigorous methods for handling missing data, by first examining the degree and patterns of missingness and identifying factors that affect the missing rates. We will adopt appropriate statistical methods, such as multiple imputation and inverse probability weighting, under plausible assumptions about the missing mechanism.

**Research Design Considerations.** There are possible threats to recruitment, which the study team has anticipated and has put into place plans to handle. *Individuals not wanting to participate*: To maximize participation, all staff involved in recruitment will be trained in motivational interviewing to increase the likelihood of participation. Individuals who opt to participate in the program will also be given a financial incentive to provide compensation for their time. In cases where individuals refuse participation in the program, we will ensure standard care is provided to ensure some services are rendered.

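### Covariates for the sensitivity analyses are chosen by baseline significance tests, so a chance p-value, not prognostic strength, decides which suspected predictors are adjusted for

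*Protocol*

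**What the plan says.** All of this stands in the Protocol, in the Statistical Analysis paragraph under Study Flow, unless noted.

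- **Primary model.** Its covariates are named in advance: "the regression model will be adjusted for race/ethnicity, biological sex, and age". Case manager is added as a fixed factor.
- **Candidate pool.** After conceding that imbalance can arise by chance, the protocol says: "Descriptive statistics for baseline characteristics known or suspected to be associated with outcomes will be prepared for the two randomization groups".
- **Tests.** "Chi-square statistics and Wilcoxon rank sum tests will be used to evaluate baseline differences between the arms for categorical and continuous variables, respectively".
- **Selection rule.** "Any variables with baseline differences will be adjusted in secondary sensitivity analyses".

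No other criterion for a baseline difference is given, neither a size of difference nor a measure of association with outcome. No cut-off is stated for these tests. The only alpha in the paragraph, "A two-sided alpha of 0.05 will be used to determine statistical significance", follows directly on the primary model. Allocation, described under Randomization Procedure, is computer-generated and concealed: "the randomization module will utilize a blocked randomization procedure with varying block sizes".

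**The concern.** When allocation is random and concealed, every baseline difference between the arms is due to chance. A test of whether it is due to chance therefore answers no open question. How far an imbalance moves the treatment estimate depends on two things: the size of the observed difference and the strength of the covariate's effect on outcome. The baseline p-value reflects the first, scaled by sample size, and carries no information on the second.

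What is at stake is the value of the sensitivity analysis. It is meant to show that the result is robust to baseline imbalance. Under this rule its covariate set is unknown until the data are tested. It can leave out the variable whose imbalance matters most, and it may contain nothing beyond the primary model. The protocol follows a better principle for the primary model, where it gives prespecification as the reason that adjustment helps.

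**Working it through.** The plan gives no figure for this rule, so there is none to reproduce. The check asks what the rule does at the planned sample size.

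**Inputs**
- 137 per arm (Sample Size and Statistical Power: "Under a sample size of 274 (137 in each arm) and allowing up to 35% attrition during the follow-up").
- Two-sided 0.05 per baseline test: an assumption, borrowed from the primary comparison.
- Number of candidates, 8 to 20, and their independence: assumptions, since the text gives neither number nor names.
- Covariate effect for the simulation, log hazard ratio 0.6 per SD: an assumption.

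**1. How large must a difference be to be flagged?** For a continuous variable, approximating the Wilcoxon test by a comparison of means:
- Standard error of the standardized difference = √(2/137) = 0.121.
- Flag threshold = 1.96 × 0.121 = 0.24 SD.
- An observed difference of 0.20 SD gives z = 0.20/0.121 = 1.66, p about 0.10: not flagged.

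The threshold is the same for a weak and a strong predictor.

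**2. How often does chance pick something?** Probability of at least one flag = 1 − 0.95^k.

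| Candidates k | At least one flagged | None flagged | Expected flags (0.05k) |
|---|---|---|---|
| 5 | 23% | 77% | 0.25 |
| 8 | 34% | 66% | 0.40 |
| 10 | 40% | 60% | 0.50 |
| 15 | 54% | 46% | 0.75 |
| 20 | 64% | 36% | 1.00 |

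Where none is flagged, the sensitivity analysis has no added covariates. Correlation among the candidates would change these percentages but not the expected number of flags.

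**3. What is left uncorrected?** A simulation of 4,000 trials used the protocol's control-arm rates (42% at one year, 59% at two), visits at 3, 6, 9 and 12 months, 35% dropout spread uniformly over the year, no treatment effect, and one covariate with the assumed effect.
- The covariate was flagged in about 5% of trials, as it must be under randomization.
- In the 646 unflagged trials with baseline p between 0.05 and 0.20, leaving the covariate out moved the log hazard ratio by about 0.10 on average, a factor of e^0.10 = 1.11 on the hazard ratio. The standard deviation of the estimate was about 0.20, so the shift is about half of that.

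**4. Does the rule damage error control?** In the same simulation type I error was 0.052 with no adjustment, 0.053 with the covariate always adjusted, and 0.050 under test-then-adjust. All agree with 0.05 within simulation error, √(0.05 × 0.95/4000) = 0.003.

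**5. How many events are there to support extra covariates?** Under the protocol's own assumptions a hazard ratio of 0.50 takes 42% to 1 − 0.58^0.5 = 23.8%. Events with no attrition = 137 × (0.42 + 0.238) = 90. If all 35% were lost at the start, 90 × 0.65 = 59. Uniform dropout gave 74 in simulation.

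**The case against.** **The pool is already prognostic.** A reader might infer that the rule ignores whether a variable predicts firearm violence and lets in irrelevant ones. The text does not support that. The sentence before the tests limits the characteristics to those with a known or suspected link to outcome, and the tests are naturally read as applying within that set. What stands is narrower: inside the pool, strength of prediction plays no part in who is adjusted for.

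**The primary result is safe.** A reader might infer bias or error inflation in the main comparison. Neither follows. The primary covariates are prespecified, the rule touches only secondary sensitivity analyses, and the simulation shows no type I error inflation. This objection stands in full and sets the weight of the point.

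**A flag is not an error.** A flagged variable has a real imbalance in the sample, and adjusting for it does not bias the treatment effect. The 34% to 64% therefore measures how far chance decides the covariate set, not a rate of harm.

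**Power of the baseline test.** It is tempting to say that a 0.2 SD imbalance would be flagged 38% of the time. That is the power against a true population difference, which cannot exist under randomization. The imbalance that matters is the observed one, and at the assumed cut-off an observed 0.2 SD would simply not be flagged.

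**The analysis plan may give the list.** A list of sensitivity covariates and a definition of a baseline difference can properly be left to a statistical analysis plan, which is not at hand. Their absence here is no fault. But the protocol itself fixes the method of selection, and an analysis plan that followed it would inherit that method.

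**Conclusion.** The point holds as a modest one. The protocol selects covariates for its secondary sensitivity analyses by testing for differences that randomization already makes a matter of chance. At 137 per arm and an assumed 0.05 cut-off, observed imbalances below about 0.24 SD stay unadjusted however strong the predictor. With 8 to 20 independent candidates (assumption), chance flags at least one in 34% to 64% of trials and leaves the analysis without added covariates in the remaining 36% to 66%. The 1.11-fold shift in the hazard ratio rests on an assumed covariate effect and on a selected subset of simulated trials. It shows what the rule can miss and is not a forecast.

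That selection is by statistical significance is the natural reading of two adjacent sentences, although no cut-off is written. The documents do not support any claim against the primary analysis, its error rate or the sample size. This is a cheap improvement, not a defect that threatens the trial's conclusion.

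**What to change.** Delete the sentence on baseline tests and the rule that follows it. Replacement wording could be: *Baseline characteristics will be summarized by arm without significance tests. A sensitivity analysis will additionally adjust for a short list of prognostic baseline variables, fixed before unblinding and included regardless of observed imbalance.* The list itself can sit in the statistical analysis plan. The protocol already intends to identify characteristics linked to outcome, so the list can be drawn from those.

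The cost is wording only. No sample size or power figure changes, and there is slightly less analysis to do. The one constraint is length. With roughly 59 to 90 events expected under the protocol's assumptions, and race/ethnicity, sex, age and case manager already in the model, the added variables must be few.
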